# A mechanism-based proof of concept study on the effects of duloxetine in patients with painful knee osteoarthritis

**DOI:** 10.1186/s13063-021-05941-y

**Published:** 2021-12-27

**Keywords:** Quantitative sensory testing, Chronic pain, Osteoarthritis, Duloxetine

## Abstract

**Background:**

The global burden of osteoarthritis (OA) is steadily increasing due to demographic and lifestyle changes. The nervous system can undergo peripheral and central neuroplastic changes (sensitization) in patients with OA impacting the options to manage the pain adequately. As a result of sensitization, patients with OA show lower pressure pain thresholds (PPTs), facilitated temporal summation of pain (TSP), and impaired conditioned pain modulation (CPM). As traditional analgesics (acetaminophen and non-steroidal anti-inflammatory drugs) are not recommended for long-term use in OA, more fundamental knowledge related to other possible management regimes are needed. Duloxetine is a serotonin-noradrenalin reuptake inhibitor, and analgesic effects are documented in patients with OA although the underlying fundamental mechanisms remain unclear. The descending pain inhibitory control system is believed to be dependent on serotonin and noradrenalin. We hypothesized that the analgesic effect of duloxetine could act through these pathways and consequently indirectly reduce pain and sensitization. The aim of this mechanistic study is to investigate if PPTs, TSP, CPM, and clinical pain parameters are modulated by duloxetine.

**Methods:**

This proof of concept study is a randomized, placebo-controlled, double-blinded, crossover trial, which compares PPTs, TSP, and CPM before and after 18 weeks of duloxetine and placebo in forty patients with knee OA. The intervention periods include a titration period (2 weeks), treatment period (60 mg daily for 14 weeks), and a discontinuation period (2 weeks). Intervention periods are separated by 2 weeks.

**Discussion:**

Duloxetine is recommended for the treatment of chronic pain, but the underlying mechanisms of the analgesic effects are currently unknown. This study will investigate if duloxetine can modify central pain mechanisms and thereby provide insights into the underlying mechanisms of the analgesic effect.

**Trial registration:**

ClinicalTrials.govNCT04224584. Registered on January 6, 2020. EudraCT 2019-003437-42. Registered on October 22, 2019. The North Denmark Region Committee on Health Research Ethics N-20190055. Registered on October 31, 2019.

## Background

Osteoarthritis (OA) is highly prevalent in the elderly population, and the prevalence of OA increases with increasing age and obesity, and thereby the prevalence is expected to rise [12]. Duloxetine is a serotonin and norepinephrine reuptake inhibitor and is currently approved for patients with knee OA and recommended by the Osteoarthritis Research Society International (OARSI) for use in patients with knee OA and widespread pain and/or depression [10]. Six randomized controlled trials have been conducted on the efficacy of duloxetine in patients with OA, which have all demonstrated analgesic effects favoring duloxetine over placebo [17] with an effect size of 0.55 [42]. The underlying mechanisms of the analgesic effects in OA remain largely unknown. Yarnitsky et al. 2012 [61] administered duloxetine to patients with diabetic neuropathies and found a stronger analgesic effect in patients having impaired conditioned pain modulation (CPM) prior to treatment, indicating that patients with a neuropathic pain-like component might respond better to duloxetine.

Recent reviews have concluded that a neuropathic pain-like component is present in subpopulations of patients with OA [20, 33, 38]. Lower pressure pain thresholds (PPTs) at the knee and remotely from the knee are found in patients with severe knee OA compared with healthy subjects, indicating localized and widespread pressure hyperalgesia [3, 6]. Temporal summation of pain (TSP) is a proxy for central nervous system excitability [50]. TSP is facilitated in severe knee OA patients compared with healthy subjects [4, 6] and has been found to be a predictor of chronic postoperative pain [32, 43, 47]. TSP has also been found to be a predictor of limited analgesic effect of non-steroidal anti-inflammatory drugs (NSAIDs) [46] in OA. CPM is a proxy for descending pain inhibitory control [60], is impaired in severe patients with OA [6] and impaired CPM has been associated with higher levels chronic postoperative pain [34, 57] and poor analgesic effects to NSAIDs effects in patients with OA [21, 48].

Limited evidence is currently available on how to treat sensitization in OA patients, but emerging indications suggest that duloxetine might be such a treatment [61].

It is expected that patients with OA pain may benefit from the duloxetine therapy as a central modulator of pain processing [6].

This proof-of-concept randomized placebo-controlled double-blinded crossover trial aimed to investigate the effect of 18 weeks of duloxetine on mechanistic pain profiles when comparing to placebo in patients with severe OA. The primary objective was to assess the treatment effect on mechanistic pain profiles (PPTs, TSP and CPM) when comparing duloxetine to placebo.

## Methods and Analysis

### Study design

This proof of concept study is a randomized, placebo-controlled, double-blinded, crossover trial, which compares PPTs, TSP, and CPM before and after 18 weeks of duloxetine and placebo. Forty patients will be randomized to one of two equally sized sequences: (1) duloxetine followed by placebo or (2) placebo followed by duloxetine (Fig. 1). Patients will be screened for inclusion (visit 1) and assessed at baseline (visit 2 and visit 4) and after the intervention (visit 3 and 5).

**Fig. 1 Fig1:**
[figure not shown]
Study design and timeline. Patients are randomized to either duloxetine followed by placebo (sequence 1) or placebo followed by duloxetine (sequence 2). Approximate dates for each study event (visits or phone calls) are highlighted in the timeline. Abbreviations: DLX, duloxetine; PBO, placebo; QD, daily dose

Randomization is conducted before baseline measurements at visit 2. During the visits, the patients will be assessed using quantitative sensory testing (QST) and questionnaires. In addition, patients are continuously asked to rate adverse events using a daily diary and the diary is assessed at each visit. Please find a complete outline of the intervention periods and assessments in Fig. 2.

**Fig. 2 Fig2:**
[figure not shown]
A Standard Protocol Items: Recommendations for Interventional Trials (SPIRIT) schematic diagram of the interventions and assessments in the trial

### Study Population and implementation

Patients are recruited through Synexus, Aalborg, Denmark (a contracting research organization). Women and men, 40–75 years of ages, with OA of the knee, who are eligible to be included in the study, agree to participate and fill in an informed consent, will be included. Patients fulfilling the inclusion criteria will be invited to a screening visit (visit 1) where a physical and psychological examination (for evaluation of suicidal risk) will be conducted by a medical doctor. The screening includes x-ray of the knee, screening of medical records, and screening of the eligibility criteria and will be handled by Synexus, Aalborg, Denmark.

Patients will be asked to discontinue the use of all analgesic pain medication (including NSAIDs) during the entire trial and any need of rescue medication (paracetamol) must be noted in the diary.

Patients who are eligible according to the inclusion and exclusion criteria will be invited to visit 2 where they will be included in the study and randomized.

Following visits 1, the entire trial including all patient communication and randomization will be handled by MechSense, Department of Gastroenterology and Hepatology, Aalborg University Hospital, Denmark.

The allocation sequence will be generated by the Hospital Pharmacy at Aarhus University Hospital, Aarhus, Denmark, and all study personal (except dedicated staff at the hospital pharmacy) and patients are blinded to the allocation sequences.

### Inclusion criteria and exclusion criteria

#### Inclusion criteria

Patients diagnosed with unilateral or bilateral OA of the knee according to the American College of Rheumatology (ACR) criteria based on clinical and radiographic evidence [1] will be recruited. In addition, patients must provide written informed consent and abide by the study restrictions. The patients must have a Kellgren and Lawrence grade of I, II, or III at the index knee. Worst pain within the last 24 h must be 5.0 cm to 10.0 cm (assessed on a 0–10-cm VAS scale anchored at 0 cm: no pain and 10 cm: worst pain imaginable) prior to enrolment. patients must agree to maintain the same activity level throughout the course of the study.

#### Exclusion criteria

Enrolment is restricted to people aged 40 years or older because knee pain in younger patients is mainly due to trauma rather than to naturally occurring OA. Patients are screened for suicidal risk using the Columbia-Suicide Severity Rating Scale [49] and patients at risk are excluded to ensure patient welfare. Interactions with other drugs are essentially unknown. Therefore, patients having specific medical conditions other than OA or taking specific medications other than the allowed are excluded because of the potential interaction of those conditions or medications with known or potential effects on duloxetine. Patients taking certain psychoactive medications, abusing drugs or alcohol, or having other dependencies are excluded because of the potential confounding factors of these medications/substances on the results.

Since the purpose of the study is to evaluate the mode of action of duloxetine in treating the pain of osteoarthritis of the knee, patients with other conditions that might produce pain in or alter the perception of the osteoarthritic pain in the index knee are excluded to avoid confounding the assessment of the primary outcome measure.

### Removal of patients

Patients will be informed that they are free to discontinue from the study at any time and for any reason. The investigator may remove a patient from the study in case of any clinical adverse event, laboratory abnormality, or current illness, which in the opinion of the investigator indicates that continued participation in the study is not in the best interest of the patient. Patients may be discontinued due to a change in compliance with inclusion/exclusion criteria that is clinically relevant and affects patient safety, occurrence of adverse events, or ingestion of non-permitted concomitant medication that might affect the patient safety or study assessments/objectives.

In case of premature discontinuation of study participation, efforts will be made to conduct all end-of-study assessments. All patients who prematurely discontinue will be followed for ongoing and newly occurring adverse events.

### Interventions

Study interventions are duloxetine treatment and placebo treatment. Patients are block-randomized (four patients at a time) to either sequence 1 (e.g., duloxetine followed by placebo) or sequence 2 (e.g., placebo followed by duloxetine). All patients will be administered an equal number of capsules containing duloxetine or placebo. Patients are thoroughly instructed on the most common adverse events and on how to report these.

Treatment periods include 2-week titration periods (week 1 (7 days): 20 mg/daily, week 2 (7 days): 40 mg/daily), a 14-week full treatment period (week 3–16 (70 days): 60 mg/daily) followed by a 2-week discontinuation period (week 17 (7 days): 40 mg/daily, week 18 (7 days): 20 mg/daily). The treatment periods are separated by at least two weeks.

The patients are instructed to take one capsule of study drug orally with approximately 200 mL of water at room temperature after breakfast in the morning of each dosing day.

### Blinding

The study drug is encapsulated in a gelatin capsule (DBCaps® from Capsugel, size: AAEL, color HPMC Swedish Orange Opaque) with identical size, color, and weight to ensure blinding.

The study drug is produced and labeled by the Hospital Pharmacy at Aarhus University Hospital. The blinding and randomization procedures are conducted by the Hospital Pharmacy at Aarhus University Hospital, Aarhus, Denmark. Patients, study personnel, and study management will be blinded until the end of the trial. Unblinding will take place if the patient’s safety is at risk to ensure allocation concealment.

### Adverse events

The principal investigator is responsible for monitoring the safety of the patients who have entered this study and for alerting Sponsor of any serious adverse event. Adverse events will be monitored from the time when the patient has signed the informed consent form and until two weeks after the last drug administration (end of study).

### Ancillary and post-trial care

If the participant should become ill or suffer injury as a direct result of the study drug or experimental procedure, he/she must inform the clinical investigator who will arrange for the proper treatment and help with further developments. This also applies if the participant will complain about the treatment.

The patients are covered by Aalborg University Hospital Patient Insurance.

### Outcomes

#### Primary outcome

The primary outcome parameters are the effects of duloxetine on experimental pain stimulations (pressure pain thresholds, cuff pain detection and tolerance thresholds, temporal summation of pain, and conditioned pain modulation).

##### Pressure pain threshold

Quantitative sensory testing of joint pain will be determined by assessing PPTs from three knee joint locations at the most painful side (the index knee). A hand-held pressure algometer (Somedic) will be used for measuring PPTs. The probe (1 cm^2^) will be placed perpendicularly to the skin and pressure will be applied until the patient defines the pressure as pain and presses a button. Spreading sensitization will be assessed by PPTs from tibialis anterior of the most painful knee and from the extensor brachii radialis muscle on the ipsilateral side. PPTs will be measured twice on each site and the mean of the two measurements will be used in the statistical analysis.

##### Cuff pain detection and tolerance threshold

Deep tissue pain sensitivity will be evaluated by cuff pressure stimuli using a computer-controlled cuff algometer (Cortex Technology and Aalborg University, Denmark) including a 13-cm wide tourniquet cuff (VBM, Sulz, Germany) and an electronic VAS (Aalborg University, Denmark) for recording of the pain intensity. The cuff will be placed at the level of the head of the gastrocnemius muscle of the lower leg at the index knee. The electronic continuous VAS (sliding resistor) is 10 cm long and sampled at 10 Hz; 0 cm indicates “no pain” and 10 cm indicates “maximum pain.” Cuff algometry is a reliable assessment for PPTs, TSP, and CPM [24, 30] and has often been utilized in studies with OA patients [32, 44, 46, 48].

The pressure of the cuff is increased by 1 kPa/s and the patient will be instructed to rate the pain intensity continuously on the electronic VAS until the tolerance level is reached. The patient will be instructed to press a stop button at this point. The pressure pain detection threshold (cPDT) is defined as the pressure at which the VAS score exceeds 1 cm. The pain tolerance threshold (cPTT) is defined when the patient presses the stop button. The measurements will be conducted once on both the ipsilateral and contralateral lower leg to the most OA-affected knee.

##### Temporal summation of pain

Ten short-lasting stimuli (1 s each) at the level of the cPTT will be given at the lower leg with a 1 s break between stimuli. The participants are instructed to continuously rate the pain intensity of the sequential stimuli using the electronic VAS and not return to zero during the breaks. For each cuff stimulus, a VAS score will be extracted.

##### Conditioned pain modulation

The CPM magnitude is assessed as the absolute changes in cPDT with and without a cuff conditioning stimulus. A conditioning stimulus will be applied to the contralateral lower leg and the cPDT will be assessed on the ipsilateral lower leg as described above. The conditioning stimulus is applied as a constant stimulus with an intensity of 70% of the pain tolerance level on the contralateral leg.

#### Secondary outcome

Secondary outcomes are assessed to evaluate the effect of duloxetine and placebo on clinical pain intensities and quality, function of the knee, quality of sleep, pain catastrophizing, anxiety, and depression, as described below.

Patients will rate the pain severity for worst pain during the day and pain severity at night on a 10 cm VAS scale. Pain severity will be recorded on a daily basis by the patients in the patient diary.

##### Pain Quality Assessment Scale

This measure begins with an introduction stating that people experience pain sensations differently and explaining how pain unpleasantness differs from pain intensity. After the introduction, the patients are asked to rate the severity of each of the 20 pain domains using 0 to 10 numerical rating scales in which 0 = ”no pain” or “no (sensation/item)” and 10 = “the most (descriptor) pain sensation imaginable.” As mentioned above, the pain domains assessed include two global domains (pain intensity and unpleasantness), two spatial domains (deep and surface), and 16 quality domains (sharp, hot, dull, cold, sensitive, tender, itchy, shooting, numb, electrical, tingling, cramping, radiating, throbbing, aching, and heavy).

##### Pittsburgh Sleep Quality Index

The Pittsburgh Sleep Quality Index is a self-rating questionnaire resulting in a global score between 0 and 21. The questionnaire consists of seven sub-scores (sleep quality, sleep onset latency, sleep duration, sleep efficiency, sleep disturbances, use of sleeping medication, and daytime dysfunction) [16].

##### The Brief Pain Inventory

The Brief Pain Inventory [18, 55] (severity and interference scores) is a self-reported scale that measures the severity of pain and the interference of pain on function. The scores range from 0 (no pain) to 10 (pain as severe as you can imagine). Four questions assess the worst pain, least pain, and average pain in the past 24 h, and the pain right now. The interference scores range from 0 (does not interfere) to 10 (completely interferes). Seven questions assess the interference of pain in the past 24 h for general activity, mood, walking ability, normal work, and relations with other people, sleep, and enjoyment of life.

##### Investigator Global Impression of Changes

The Investigator Global Impression of Changes is a questionnaire used by physicians to provide a global impression of change in the patient’s health whether or not it is related to observational study treatment. The Investigator Global Impression of Changes is often used to show that a change in the patient is clinically meaningful. This instrument asks the physician to answer the following question, “Compared to the patient‘s condition at admission to this study, how much has he or she changed?” on a seven-point scale with + 3 equaling very much improved and − 3 equaling very much worse [26]. The Investigator Global Impression of Changes and other global impression questionnaires have a long history of use across a number of therapeutic areas and indications.

##### Patient Global Assessment of Changes

This questionnaire assesses the change in their health status since beginning the study treatment. Like the Investigator Global Impression of Changes, the Patient Global Assessment of Changes has been used frequently in clinical and observational studies across the spectrum of therapeutic areas and products. The Patient Global Assessment of Changes is useful in assessing whether the impact of the study treatment is meaningful enough to give value to the patient [56].

##### Western Ontario and McMaster Osteoarthritis Scale

The Western Ontario and McMaster Osteoarthritis Scale [11] is a patient-rated instrument that measures OA symptoms. The questionnaire contains five pain questions, two stiffness questions, and 17 physical function questions (24 questions total). Each question utilizes a 5-point scale from 0 (none) to 4 (extreme).

##### PainDetect-Questionnaire

The PainDetect Questionnaire has been developed to assess the neuropathic components of a given pain disease [23]. The PainDetect-Questionnaire is a validated, easy to use, screening tool that predicts the likelihood of a neuropathic pain component in chronic pain disorders [23]. It shows higher sensitivity and specificity in comparison with other neuropathic pain screening questionnaires.

##### The Pain Catastrophizing Scale

The Pain Catastrophizing Scale consists of 13 items focusing on thoughts and feelings in connection with pain [54]. The questions are to be rated on a 4-point scale ranging from 0 (not at all) to 3 (very much).

##### Hospital Anxiety and Depression Scale

Anxiety and depression symptoms are assessed using the Hospital Anxiety and Depression Scale (36), which applies a subscale for anxiety and a subscale for depression. The Hospital Anxiety and Depression Scale ranges from 0 to 21: 0 to 7 indicate no symptoms of anxiety/depression, 8 to 10 indicate possible symptoms of anxiety/depression, and 11 to 21 indicate severe symptoms of anxiety/depression [62].

##### Sample size

Wang et al. 2019 [2] demonstrated an effect size of 0.55 when assessing the worst pain within the last 24 h for 10-week treatment of duloxetine compared with placebo in a parallel design with patients with moderate-to-severe OA. It is believed that the effect of duloxetine acts through descending pain pathways and therefore the decrease in pain intensity must be associated with the modulation of pain mechanisms. A sample equation with 85% power and a significant level at 0.05 using a crossover design yields 32 patients. Forty patients will be enrolled to account for potential drop-outs.

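### The stated 85% power rests on worst pain, a secondary outcome, and is not established for any of the QST primary outcomes

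*Protocol article*

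**What the plan says.** The Sample size section of the protocol article starts from a published trial that "demonstrated an effect size of 0.55 when assessing the worst pain within the last 24 h". That result came from "10-week treatment of duloxetine compared with placebo in a parallel design". The section then states a belief that duloxetine acts through descending pain pathways and concludes that "therefore the decrease in pain intensity must be associated with the modulation of pain mechanisms". The calculation follows: "A sample equation with 85% power and a significant level at 0.05 using a crossover design yields 32 patients". Enrolment is then raised: "Forty patients will be enrolled to account for potential drop-outs".

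The outcome sections rank the measures differently from the sample size. Under Primary outcome: "The primary outcome parameters are the effects of duloxetine on experimental pain stimulations", namely PPT, cuff detection and tolerance thresholds (cPDT, cPTT), TSP and CPM. The Primary outcomes paragraph of the Statistical analysis plan section compares changes from baseline in the same measures. Under Secondary outcome: "Secondary outcomes are assessed to evaluate the effect of duloxetine and placebo on clinical pain intensities and quality". Worst pain appears there twice, once in the daily diary and once in the Brief Pain Inventory.

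**The concern.** The power statement should belong to the outcomes that carry the primary objective. Here its only numerical input is the effect on a clinical pain score, and one sentence of reasoning carries it over to five experimental pain measures. That sentence has two weaknesses.

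- It treats as settled what the trial is meant to find out. The abstract says that "analgesic effects are documented in patients with OA although the underlying fundamental mechanisms remain unclear" and presents action through these pathways as a hypothesis. The Background section calls the mechanisms largely unknown, and the Discussion says only that the trial may possibly link mechanism to analgesia.
- Even a true association between pain relief and mechanism change says nothing about the size of the standardised effect on a pressure threshold, a series of cuff pain ratings or a change in detection threshold. Each has its own variance.

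What is at stake is how a null result is read. The Discussion expects the trial to show whether the sensitised pain system can be modified by duloxetine. If power for the QST measures is unknown, a non-significant QST result cannot be told apart from too few patients.

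**Working it through.** **Inputs from the Sample size section.** Effect size 0.55 (worst pain, parallel design, 10 weeks); power 85%; significance level 0.05, sidedness not stated; crossover; 32 patients, raised to 40 (implied drop-out allowance 8/40 = 20%). The article gives no effect size, SD or correlation for any QST measure.

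**Step 1: reproduce the plan's figure.** Take a paired t-test on the within-patient difference, with standardised effect dz = mean difference / SD of the difference. Power is the probability that a noncentral t variable with n − 1 degrees of freedom and noncentrality dz × √n exceeds the two-sided 5% critical value in absolute size. At dz = 0.55 and n = 32 the noncentrality is 0.55 × √32 = 3.11.

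- n = 31 gives 84.2% and n = 32 gives 85.4%, so 32 is the smallest n that reaches 85%.
- With n − 2 degrees of freedom (2×2 crossover), n = 32 gives 85.3%.
- The normal approximation is ((1.960 + 1.036)/0.55)² = 29.7, or 30.
- A one-sided test gives 26, which does not match, so two-sided is assumed below.

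The arithmetic is right, and it uses 0.55 directly as dz.

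**Step 2: what using 0.55 as dz assumes.** A parallel-group effect is scaled by the between-patient SD. For a difference of two measurements per patient with correlation ρ, dz = 0.55 / √(2(1 − ρ)).

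| ρ | dz | N for 85% | power at 32 |
|---|---|---|---|
| 0 | 0.389 | 62 | 57% |
| 0.3 | 0.465 | 44 | 72% |
| 0.5 | 0.550 | 32 | 85% |
| 0.7 | 0.710 | 20 | 97% |

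So 32 patients gives 85% power for worst pain itself only at ρ = 0.5, which the article does not state.

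**Step 3: power for QST measures over an assumed range.** The dz values are assumptions, because the article gives none. Two-sided 0.05, no multiplicity adjustment.

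| assumed QST dz | power at 32 | power at 40 | N for 85% |
|---|---|---|---|
| 0.20 | 20% | 24% | 227 |
| 0.30 | 38% | 46% | 102 |
| 0.40 | 59% | 69% | 59 |
| 0.50 | 78% | 87% | 38 |
| 0.55 | 85% | 92% | 32 |

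If the QST effect were half the pain effect (0.5 × 0.55 = 0.275), power at 32 would be about 33% and N for 85% would be 121.

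**Step 4: detectable effect.** Solving for dz at 85% power gives 0.547 at n = 32 and 0.486 at n = 40.

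**Step 5: the unit of that effect.** The Statistical analysis plan section compares changes from baseline, and Study design gives each period its own baseline (visits 2 and 4). If simple change scores are used, the contrast is (duloxetine end − its baseline) − (placebo end − its baseline), which has four measurements. With independent errors of variance σ², its variance is 4σ², against 2σ² for a test-retest difference. The SD ratio is √(4/2) = 1.41. Converting 0.55 or 0.49 to kPa or VAS with a test-retest SD would then understate the detectable effect.

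**The case against.** Four points can be made for the plan.

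- **A reader might infer that no primary outcome has 85% power, or that the trial is underpowered for QST.** The documents do not support that. They give no QST effect or SD, and any QST measure with a within-patient effect of at least about 0.55 at 32 completers, or 0.49 at 40, would have 85% power. The lower figures in the working show a risk over an assumed range; they do not measure a shortfall. This point stands and limits the conclusion to power that is not established.
- **The source is disclosed.** The section says openly that 0.55 concerns worst pain in a parallel design, and it never says in so many words that each QST measure has 85% power. That is true. But the sentence linking pain to mechanism serves only to carry the calculation over to the primary outcomes, so the inference is the natural one.
- **A proof-of-concept study may be sized on a related clinical effect, and the full protocol may say more.** Both are fair. They limit the criticism to what the article prints and lower its severity. They do not make the printed reason valid: the article treats the same link as open elsewhere.
- **The Discussion hedges.** It says mechanism and analgesia will possibly be linked. The hedge covers the link, but not the expectation that the trial can show whether the pain system is modifiable.

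It is also tempting to say that 85% is at least sound for worst pain. Step 2 of the working shows that this too rests on an unstated correlation.

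**Conclusion.** The point holds in a limited form: the 85% power is not established for any primary outcome. The figure rests on a 0.55 effect for a secondary outcome from a parallel-group trial. It is carried to the QST primaries by an asserted association that the trial itself sets out to test and that would not fix the size of their effects.

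What can be said for the primaries is the detectable effect: about 0.55 SD of the within-patient contrast at 32 completers and 0.49 SD if all 40 complete. This assumes a paired t-test, 85% power, two-sided 0.05 and no adjustment for five measures. Whether true QST effects are that large cannot be judged from the article. The wording should be corrected, but sample size, outcomes and analysis need not change on this account.

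**What to change.** In Sample size:

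1. Remove the asserted association as the basis of the power claim.
2. Say that 32 patients gives 85% power only for a within-patient standardised effect of 0.55, two-sided 0.05, and that this value comes from a parallel-group worst-pain result and so assumes a within-patient correlation of 0.5.
3. For PPT, cPDT, cPTT, TSP and CPM, replace the power claim with the smallest effect detectable with 85% power at two-sided 0.05, unadjusted for multiplicity: about 0.55 SD at 32 completers and 0.49 SD at 40. State the unit as the SD of the duloxetine-minus-placebo contrast actually analysed.
4. Base any conversion to kPa or VAS on the SD of that contrast (change from each period's baseline), not on a simple test-retest SD.

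In the Discussion section on underlying mechanisms, soften the statement of what the trial will be able to show, so that a non-significant QST result is read through its 95% confidence interval and not as absence of a mechanism.

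Cost: text only, no extra patients. The plan gives up a favourable power claim for its primary outcomes.
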